### 5.2.7. Dose modification for increases in ALT and/or AST

Dose modifications required for study drug-related increases in ALT and/or AST concentrations and requirements for monitoring are provided in Table 4. During the first 2 cycles of treatment, ALT, AST, and bilirubin must be obtained at baseline and monitored weekly (ie, on Days 1, 8, 15, and 22 of Cycles 1 and 2 [ $\pm$ 3 days]), even if values are normal. The investigators may use investigational site or local laboratory AST, ALT, and bilirubin values for subject treatment decisions for Days 8 and 22 of Cycles 1 and 2; these values must be entered in the eCRF

**Table 4: Dose modification/interruption for alanine aminotransferase and/or aspartate aminotransferase increases related to study drug**

| Increases in AST/ALT (CTCAE v 4.0)                                                                           | 1st occurrence                                                                                                                                                                                                                                | Restart                                                                                                                                                                               | Recurrence |
|---------------------------------------------------------------------------------------------------------------------|------------------------------------------------------------------------------------------------------------------------------------------------------------------------------------------------------------------------------------------------------|----------------------------------------------------------------------------------------------------------------------------------------------------------------------------------------------|-------------------|
| AST and/or ALT $\leq 5 \times \text{ULN}$ ( $< \text{Grade } 3$ )                                                   | Continue dosing, with weekly monitoring of liver function until transaminases return to $< 3 \times \text{ULN}$ ( $\leq \text{Grade } 1$ ) or baseline.                                                                                              |                                                                                                                                                                                              |                   |
| ALT and/or AST $> 5 \times \text{ULN}$ ( $\geq \text{Grade } 3$ )                                                   | Interrupt dosing, with weekly monitoring until transaminases return to $< 3 \times \text{ULN}$ or baseline.                                                                                                                                          | If the potential benefit for reinitiating regorafenib is considered to outweigh the risk of hepatotoxicity: reduce 1 dose level and measure serum transaminases weekly for at least 4 weeks. | Discontinue.      |
| ALT and/or AST $> 20 \times \text{ULN}$ ( $\geq \text{Grade } 4$ )                                                  | Discontinue.                                                                                                                                                                                                                                         |                                                                                                                                                                                              |                   |
| ALT and/or AST $> 3 \times \text{ULN}$ ( $\geq \text{Grade } 2$ ) with concurrent bilirubin $> 2 \times \text{ULN}$ | Discontinue treatment and measure serum transaminases weekly until resolution.
Exception: subjects with Gilbert's syndrome who develop elevated transaminases should be managed as per the recommendations outlined above for ALT/AST elevations. |                                                                                                                                                                                              |                   |

ALT, AST, and bilirubin must be obtained at baseline and monitored weekly for the first 2 cycles (ie, on Days 1, 8, 15, and 22 of Cycles 1 and 2 [ $\pm 3$  days]), even if values are normal. The investigators may use investigational site or local laboratory AST, ALT, and bilirubin values for subject treatment decisions for Days 8 and 22 of Cycles 1 and 2; these values must be entered in the eCRF.

### 5.2.8. Dose modification/interruption and management of treatment-emergent hypertension

Blood pressure (BP) should be monitored on every visit. The recommendations for dose modification/interruption and management of treatment-emergent hypertension are summarized in Table 5. Management includes a stepped-care approach to the control of BP as well as dose modification of the study drug if required. The selection of antihypertensive medication used in this setting will be made at the investigator's discretion, considering possible site-specific guidelines. All antihypertensive medications must be entered in the subject's Concomitant Medication eCRF.

**Table 5: Dose modification/interruption and management of treatment-emergent hypertension**

| Severity Grade (CTCAE v4.0) | Definition                                                                                                                                       | Antihypertensive therapy                                                                                                                                                                                   | Dose modification/interruption                                                                                                                                                                                                                                                                                                                               |
|-----------------------------|--------------------------------------------------------------------------------------------------------------------------------------------------|------------------------------------------------------------------------------------------------------------------------------------------------------------------------------------------------------------|--------------------------------------------------------------------------------------------------------------------------------------------------------------------------------------------------------------------------------------------------------------------------------------------------------------------------------------------------------------|
| Grade 1                     | Prehypertension:
SBP 120-139 mmHg or
DBP 80-89 mmHg                                                                                        | None                                                                                                                                                                                                       | Continue study drug.
Consider increased BP monitoring.                                                                                                                                                                                                                                                                                                    |
| Grade 2                     | SBP 140-159 mmHg or
DBP 90-99 mmHg
OR
Symptomatic increase in DBP >20 mmHg or to >140/90 mmHg if previously within normal limits | Treat with the aim to achieve DBP ≤ 90 mmHg.
If S/DBP previously within normal limits, start antihypertensive monotherapy.
If subject is taking antihypertensive medication, titrate the dosage up.  | Continue study drug.
If symptomatic, delay dose until symptoms resolve AND diastolic BP ≤ 90 mmHg. a
Restart dose at same dose level.                                                                                                                                                                                                       |
| Grade 3                     | SBP ≥ 160 mmHg or
DBP ≥ 100 mmHg
OR
≥1 antihypertensive drug or more intensive antihypertensive therapy required than previously | Treat to DBP ≤ 90 mmHg.
Start antihypertensive medication.
AND/OR
Increase dose of current antihypertensive medication.
AND/OR
Add additional antihypertensive medication(s). | Delay dose until DBP ≤ 90 mmHg and, if symptomatic, until symptoms resolve. a
Restart dose at same dose level.
If BP not controlled with more intensive therapy, reduce dose to Dose Level -1. b
If Grade 3 hypertension recurs after dose reduction and antihypertensive therapy, reduce dose to Dose Level -2. c |
| Grade 4                     | Life-threatening consequences (malignant hypertension):
transient or permanent neurologic deficit, hypertensive crisis                        | —                                                                                                                                                                                                          | Discontinue therapy.                                                                                                                                                                                                                                                                                                                                         |

In cases in which only one value is >Grade 1 (eg, 155/88 mmHg), the guidelines provided for the highest grade should be followed.

BP = blood pressure, DBP = diastolic blood pressure, SBP = systolic blood pressure.

- Subjects requiring a delay of study treatment > one cycle (4 consecutive weeks; maximum of 5 weeks between doses of regorafenib) must discontinue study drug.
- If BP remains controlled for ≥ one full cycle, dose re-escalation is permitted at the investigator's discretion.
- Subjects requiring dose reduction below Dose Level -2 (80mg) must discontinue study drug.

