### 5.2 Dose modifications and interruptions

The dose or dosing schedule of the study drug may be modified following the occurrence of a clinically significant AE that is:

- related or not related to the study drug, and
- of a pre-specified severity Grade

All dose modifications are to be made according to the pre-defined dose levels presented in Table 1.

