**Table1 : Pre-defined dose levels**

| Dose level                   | Number of tablets                    |
|------------------------------|--------------------------------------|
| Dose level 0 (standard dose) | 4 regorafenib 40-mg tablets (160 mg) |
| Dose level -1                | 3 regorafenib 40-mg tablets (120 mg) |
| Dose level -2                | 2 regorafenib 40-mg tablets (80 mg)  |

Dose reductions leading to a daily dose below Dose Level -2 (ie, fewer than 2 tablets daily) are not permitted. Treatment will be definitively discontinued if the subject is unable to tolerate a daily dose of at least two tablets.

Treatment with the study drug will be also definitively discontinued if it is necessary to interrupt the study drug treatment schedule for more than one cycle (4 consecutive weeks that is maximum of 5 weeks permitted between doses of regorafenib).

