### 5.2.3. Dose re-escalation

The maximum dose level is 0 (4 tablets daily). If dose reduction is required to Dose Level -1 (3 tablets daily) or Dose Level -2 (2 tablets daily), the dose may be re-escalated (increased) to Dose Level -1 (3 tablets daily) or Dose Level 0 (4 tablets daily) at the discretion of the investigator, provided the severity of all AEs requiring dose reduction have returned to baseline Grades after a full cycle of therapy. Dose escalation should be done one dose level at a time.

The exception to this rule occurs with toxicities associated with HFSR, also known as PPE. For subjects with HFSR, dose re-escalation may be considered, at the discretion of the investigator, after AE severity is reduced to Grade  $\leq 1$ . Additional details are provided below (*Dose modifications and supportive measures for HFSR*) and in Table 3.

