| Grade 3                      | Delay until $\leq$ Grade 2 a | Reduce by 1 dose level                                                                                | If toxicity remains $\leq$ Grade 2, dose re-escalation may be considered at the discretion of the treating investigator. If dose is re-escalated and toxicity ( $\geq$ Grade 3) recurs, institute permanent dose reduction |
| Grade 4                      | Delay until $\leq$ Grade 2 a | Reduce by 1 dose level. Permanent discontinuation may be considered at the investigator's discretion. | ---                                                                                                                                                                                                                        |

\* Excludes alopecia, non-refractory nausea/vomiting, non-refractory hypersensitivity, and non-clinically significant and asymptomatic laboratory abnormalities

a: If no recovery after one cycle (4 consecutive weeks; maximum of 5 weeks between doses of regorafenib), treatment should be permanently discontinued.

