- Dose interruption for  $\geq$  28 days (one cycle [4 consecutive weeks; maximum of 5 weeks between doses of regorafenib]) requires permanent discontinuation of study drug.
- The lowest recommended dose is 80 mg.
- If toxicity  $\leq$  Grade 1 after dose reduction for one full cycle of therapy, dose re-escalation is permitted at the investigator's discretion.

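### The dose-modification rules contradict each other in three places: the Grade 2/3 hypertension boundary, an interruption of exactly 28 days for hand-foot skin reaction, and the condition for re-escalation

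*Protocol*

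**What the plan says.** **Hypertension (Section 5.2.8, Table 5).** The Grade 2 row covers systolic pressure of 140-159 or diastolic pressure (DBP) of 90-99 mmHg. Its therapy column reads "If S/DBP previously within normal limits, start antihypertensive monotherapy"; a patient already on treatment has the dose raised. Study drug continues, with one qualification: "If symptomatic, delay dose until symptoms resolve AND diastolic BP ≤ 90 mmHg". The Grade 3 row covers 160 systolic or 100 diastolic and above, or, as an alternative, "≥1 antihypertensive drug or more intensive antihypertensive therapy required than previously". Its action is to delay the dose until DBP is 90 mmHg or lower and any symptoms have gone.

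**Interruption limit.** Section 5.2, below Table 1, ends treatment "if it is necessary to interrupt the study drug treatment schedule for more than one cycle", given as four consecutive weeks. Section 5.3 and the note to Table 5 also set the limit at more than one cycle. In Table 3, the later Grade 2 occurrences and the second Grade 3 occurrence of hand-foot skin reaction (HFSR) allow interruption of up to and including 28 days, followed by resumption. The note to that table covers interruptions of 28 days or longer and ends "maximum of 5 weeks between doses of regorafenib]) requires permanent discontinuation of study drug".

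**Re-escalation.** Section 5.2.3 permits it "provided the severity of all AEs requiring dose reduction have returned to baseline Grades after a full cycle of therapy" and names HFSR as the exception. Section 5.2.5 allows it to be considered on return to baseline. In the Grade 3 row of Table 2, if toxicity stays at Grade 2 or lower, "dose re-escalation may be considered at the discretion of the treating investigator". Section 5.2.5 makes the reduction permanent at a second Grade 3 event; Table 2 does so when toxicity recurs after re-escalation.

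**The concern.** Each pair of rules gives two answers for the same patient. A site following one passage continues, resumes or raises the dose; a site following the other holds, stops or keeps the lower dose. In a single-arm study at 5 to 10 centres, no control group absorbs such differences. They enter the description of exposure and discontinuation as if they were properties of the drug. They also leave a treating physician with conflicting safety instructions, some of them mandatory: the general interruption limit and the notes to Tables 3 and 5 are worded as requirements.

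**Working it through.** No sample-size, power or error-rate figure is involved. The check applies each rule as written to the same patients.

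**1. Table 5.** Take a patient in the Grade 2 pressure range who needs a first drug or a higher dose. The first branch is one antihypertensive drug. The second is more intensive therapy than before. Both fall within the alternative Grade 3 definition.

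| Patient | Grade 2 row | Grade 3 row | Do the actions differ? |
|---|---|---|---|
| Asymptomatic, 150/95 mmHg | continue | delay until DBP is 90 or lower | yes |
| Asymptomatic, 155/88 mmHg | continue | release condition already met | no |
| Symptomatic, 150/95 mmHg | delay until symptom-free and DBP is 90 or lower | delay on the same conditions | no |

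The conflict in action is therefore confined to asymptomatic patients with DBP above 90.

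Three provisions might have settled it, and none does. The note on following the highest grade addresses a patient in whom only one of the two pressures exceeds Grade 1. Section 5.2.2 addresses several simultaneous toxicities, not one toxicity that fits two rows. The general rule, "All dose modifications are to be made according to the pre-defined dose levels presented in Table 1", fixes the dose steps, not what triggers them.

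**2. Interruption.** One cycle is 4 × 7 = 28 days.

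| Days off drug | Table 3 rows (HFSR) | Table 3 note | Sections 5.2 and 5.3, Table 5 note |
|---|---|---|---|
| 27 | may resume | may resume | may resume |
| 28 | may resume | must stop | may resume |
| 29 | limit exceeded | must stop | must stop |

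At exactly 28 days Table 3 contradicts itself, and its note contradicts the general limit. A break of exactly one cycle is a natural resumption point, so the case is not far-fetched.

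**3. Re-escalation.** Take a non-HFSR toxicity with baseline grade 0, reduced once for Grade 3.

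| Residual grade | Section 5.2.3 (after a full cycle) | Section 5.2.5 | Table 2 |
|---|---|---|---|
| 0 | eligible | eligible | eligible |
| 1 | not eligible | not eligible | eligible |
| 2 | not eligible | not eligible | eligible |

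Now let a second Grade 3 event occur at the reduced dose, with no re-escalation in between. Section 5.2.5 makes the reduction permanent. Table 2 does not, because its trigger is recurrence after re-escalation.

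**The case against.** **Discretion.** Several of these tables are labelled recommended or suggested, and re-escalation is left to the investigator throughout. A site could satisfy every passage on re-escalation by following the strictest one. This softens the third point. It does not remove it, because discretion does not tell a site which patients are eligible, and it does not reach the mandatory stopping rules.

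**The interruption conflict is narrow.** This is correct. It concerns one day, for HFSR only, and turns on the sign in the Table 3 note. A reader might go further and infer a conflict from day 29 to day 35, because the four-week limit appears alongside a five-week maximum between doses (5 × 7 = 35). The two can be reconciled if the scheduled week off is added to the four weeks. The protocol does not say so, but neither does it contradict it, so that reading is not pressed.

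**The hypertension overlap may rest on one symbol.** If the sign before the 1 were a slip for strictly more than one drug, the monotherapy branch would no longer meet that phrase. The titration branch would still meet the wording on more intensive therapy, so the overlap would shrink but remain.

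**The toxicity endpoint.** A reader might infer that all treated Grade 2 hypertension will be reported as Grade 3. The documents do not support this. The worst grade in Section 9.2 comes from adverse events graded by CTCAE v4.0 under Section 8, and Table 5 is a guide to dose modification and management. Because its grade column carries the CTCAE v4.0 label, some sites may grade from it. That makes inconsistent grading possible, not established.

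**Conclusion.** The three contradictions stand in the current text and can be shown without any outside source. Their extent is limited:

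- **Hypertension:** the instructions on study drug differ only for asymptomatic patients with DBP above 90 mmHg.
- **Interruption:** the conflict is firm only at exactly 28 days, for HFSR.
- **Re-escalation:** it affects patients with residual toxicity above baseline but no higher than Grade 2, and those with a second Grade 3 event who have not been re-escalated.

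The protocol gives no incidence for any of these groups, so no count of affected patients out of the planned 46 can be derived.

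A reader might also infer that the 6-month progression-free rate is biased. The link is only indirect. Under Section 9.1, stopping regorafenib for an adverse event counts as a failure only if another antineoplastic treatment starts within 6 months of registration; otherwise the patient is followed to progression. The sample size and the two-stage decision rule do not depend on these passages. What is at stake is consistent patient management and interpretable exposure across centres, with possible inconsistency in hypertension grades if sites grade from Table 5. That is enough to justify a correction.

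**What to change.** The sponsor should reconcile the passages as follows:

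1. Redraw the Grade 2 and Grade 3 rows of Table 5 so that they do not overlap and the therapy ordered in one row cannot by itself place the patient in the other.
2. Make the Table 3 note agree with the Table 3 rows and with the limit in Sections 5.2 and 5.3 and the Table 5 note.
3. State one re-escalation condition, and one trigger for permanent reduction, in Sections 5.2.3 and 5.2.5 and Table 2.

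Which threshold or rule holds is for the clinical team; no view is taken here. The cost is a clarifying amendment and a notice to sites. No procedure, visit or patient is added, and the statistical design stays as it is.

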#### Special recommendations

- Recommended dose modifications for HFSR (PPE syndrome) with severity Grade  $\geq 1$  are provided in Table 3.
- Required dose modifications for ALT and/or AST increases related to study drug with severity Grade  $\geq 1$  (CTCAE v 4.0) are provided in Table 4; recommended liver function monitoring schedules are also provided.
- Recommended dose modifications for treatment-emergent hypertension with severity Grade  $\geq 1$  (CTCAE v 4.0) are provided in Table 5; general recommendations for the management of hypertension are also provided.

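### Table 5 lets a dose hold triggered by Grade 3 systolic pressure end on diastolic pressure alone

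*Protocol*

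**What the plan says.** Table 5 in Protocol section 5.2.8 sets out the management of treatment-emergent hypertension by grade. The Grade 3 definition is "SBP ≥ 160 mmHg or" a diastolic value of at least 100 mmHg, with a further route through the need for more antihypertensive treatment. These are alternatives, so systolic pressure alone suffices.

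The treatment goal in the Grade 3 row is "Treat to DBP ≤ 90 mmHg". The dosing advice is "Delay dose until DBP ≤ 90 mmHg and, if symptomatic, until symptoms resolve", followed by "Restart dose at same dose level". A conditional step comes next: "If BP not controlled with more intensive therapy, reduce dose to Dose Level -1".

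A closing note deals with readings in which only one of the two values is above Grade 1. It gives 155/88 as its example and says that "the guidelines provided for the highest grade should be followed".

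The status of the table is set in section 5.2.4, which introduces it with "Recommended dose modifications for treatment-emergent hypertension with severity Grade" 1 or higher. The same list calls the ALT/AST modifications required.

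**The concern.** The Grade 3 delay is the step that keeps regorafenib off until the pressure has come down. It works only if the value that starts the hold is also checked before the hold ends. Here the hold can start on systolic pressure but ends on diastolic pressure. For an asymptomatic patient with an isolated systolic rise, the advice followed literally gives no hold at all, and dosing resumes at an unchanged level while the reading is still in the Grade 3 range.

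The closing note shows that this is not a remote case. Its own example is a raised systolic value with a diastolic value below 90, so the table expects such patients and sends them to the higher-grade row.

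**Working it through.** No figure in the protocol needs reproducing. The check applies the Grade 3 rules to example readings, which are illustrative. All patients are asymptomatic, so the symptom condition does not apply.

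**Inputs (Table 5).** Entry: SBP ≥ 160 or DBP ≥ 100. Release: DBP ≤ 90. Dose after release: unchanged.

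| Reading | Grade 3? | Release condition | Result under the present advice |
|---|---|---|---|
| 175/85 | Yes, 175 ≥ 160 | 85 ≤ 90, already met | No hold; restart at 175 − 160 = 15 mmHg above the systolic threshold |
| 165/95 | Yes, 165 ≥ 160 | Needs a diastolic fall of 95 − 90 = 5 mmHg | Can restart at 165/90, systolic still ≥ 160 |
| 170/102, treated to 162/89 | Yes, on both values | 89 ≤ 90, met | Can restart at 162/89, systolic still ≥ 160 |

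**Is there a systolic release value elsewhere?**
- The notes under Table 5 cover discontinuation after a long delay, re-escalation and the lowest dose. None gives a systolic value.
- Section 5.3 allows the investigator to stop treatment judged harmful, without a pressure value.
- Section 6.2 sets visits and the frequency of blood pressure monitoring.
- Section 8.3 asks for two further measurements, 5 minutes apart, when the first reading is above 140/90. These are same-visit checks and set no condition for restart.
- The step to Dose Level -1 depends on pressure not being controlled under more intensive therapy. It is not a condition for ending the hold, and controlled is not defined.

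**Effect of adding SBP < 160 to the release condition.**
- 175/85 is held until systolic pressure falls by more than 15 mmHg.
- 165/95 is held until diastolic pressure falls by 5 mmHg and systolic by more than 165 − 160 = 5 mmHg.
- 162/89 is held until systolic pressure falls by more than 162 − 160 = 2 mmHg.

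**Why 160.** In the Grade 2 row, with "SBP 140-159 mmHg or" a diastolic alternative, asymptomatic patients continue the drug. A release just below 160 therefore matches the systolic level at which the table already permits dosing. A release at SBP ≤ 140 would require a fall of at least 175 − 140 = 35 mmHg from 175/85.

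**Why 160 should stop at the delay sentence.** If SBP < 160 also defined controlled pressure, 159/90 would count as controlled, and the note under Table 5 would permit re-escalation after one full cycle. Exclusion criterion 11 treats SBP above 140 as uncontrolled.

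**The case against.** The strongest reply is that the row already contains a safeguard. Its reduction step refers to blood pressure as a whole, and a patient still at 160 or more on intensified treatment is hard to call controlled. That stands as a limit on how long the situation lasts. It does not repair the hold, because the step acts only after treatment has been intensified and pressure judged again.

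The second reply is that Table 5 is advice. This also stands: an investigator who holds longer does not deviate, antihypertensive treatment is to be started or increased at once, and treatment judged harmful can be stopped.

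The third reply is that DBP ≤ 90 is a consistent anchor, since the Grade 2 row uses it too. But asymptomatic Grade 2 patients continue the drug anyway, so the Grade 2 row is not criticised here. Nor is release in patients who are Grade 3 only through the need for more therapy.

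Three stronger readings may tempt a reader:
- **A full cycle of dosing at Grade 3 pressure.** From Cycle 3 the required visits are on Day 1 only, so the next required reading could be 28 days away, with 21 dosing days. The protocol does not prescribe that gap. Section 5.2.8 describes stepped care, section 6.2 allows Day 15 visits, and the reduction step presupposes a recheck. The figure is a scheduling ceiling, not an expected exposure.
- **A protocol that demands restart at 175/85.** It allows restart; it does not oblige it.
- **A contradiction with exclusion criterion 11.** That criterion governs entry and sets no rule for patients on treatment. It matters here only as a guide to what controlled should mean.

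**Conclusion.** The gap is real and narrow. For an asymptomatic patient whose Grade 3 rests on systolic pressure with DBP ≤ 90, the recommended hold is satisfied immediately, and the row allows the same dose while the systolic value is still in the Grade 3 range. Where DBP is above 90, the hold can likewise end with systolic pressure still at 160 or more.

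The conclusion rests on the wording of Table 5 and on the absence of a systolic release value elsewhere in the protocol. The exposure before a recheck depends on site practice, and the number of patients affected cannot be derived from the document. The point concerns a dose-safety rule. A reader should not infer any effect on the sample size, the error rates or the validity of the primary analysis. It merits correction because advice followed faithfully defeats its own purpose, and the correction is small.

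**What to change.** Change only the delay sentence in the Grade 3 row: insert SBP < 160 mmHg as a joint condition with DBP ≤ 90 mmHg, and keep the symptom condition. The value is an assumption chosen to match the Grade 2 row, and the sponsor's clinicians should confirm it.

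Do not carry SBP < 160 into the treatment goal or into the meaning of controlled pressure for dose reduction and re-escalation. If those are given a systolic value, use one consistent with exclusion criterion 11, that is SBP ≤ 140. Leave the Grade 2 row and exclusion criterion 11 as they are.

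The cost is a protocol amendment to one sentence, and longer holds for some patients. Under section 5.2 and the notes to Table 5, a hold beyond one cycle means discontinuation. Under section 9.1, an interruption for adverse events counts as a primary-endpoint event if another antineoplastic treatment follows within 6 months of registration. One patient turned from success to failure in this way would move the rate by 1/46 = 2.2 percentage points, for example from 18/46 (39.1%, positive) to 17/46 (37.0%, not positive). Using < 160 rather than ≤ 140 for release keeps this risk smaller.
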